#### 2.6.2. Secondary Outcomes

##### Dietary Intake Assessment and Nutritional Adequacy

Dietary intake was assessed through a 24-h dietary recall method, including two non-consecutive days, following European Food Safety Authority recommendations [33]. A 24-h dietary recall is a structured interview that collects detailed information (time of day, food source, portion size, and preparation method) about all foods, beverages, and dietary supplements consumed by the participant in the past 24 h. A food model manual with pictures was used to help respondents judge and report portion size and improve accuracy. Information regarding nutritional supplements was also collected (such as type of supplement, name, and dosage).

Energy and nutritional intake, based on the 24 h recalled food data, were estimated using the nutritional analysis software Food Processor®, version SQL 11.11.32 (ESHA Research Inc., Salem, OR, USA).

Additionally, a Food Propensity Questionnaire [34] was applied to estimate usual and seasonal long-term dietary intake based on the preceding year. The frequency of consumption was based on the following food groups: (i) bread- and cereal-based foods, baked goods, and sugar; (ii) vegetables and fruits; (iii) nuts, seeds, and pulses; (iv) meat (including red and processed meat products); (v) fish (including oily-fish) and seafood; (vi) eggs; (vii) dairy products and substitutes; (viii) fruit juices and soft drinks; (ix) alcoholic beverages; and (x) coffee and tea. Seven potential response options were given to estimate the frequency of intake: never, <1 time per month, 1–3 times per month, one time per week, 2–3 times per week, 4–5 times per week, and 6–7 times per week.

The Mediterranean Diet Adherence Screener (MEDAS) Questionnaire [35], validated in the Portuguese population, was used to assess participants’ adherence to the Mediterranean Diet, a traditional gold model of an SHD. The total score of this questionnaire ranges between 1 and 14, in which scores greater than 9 indicate high adherence to the Mediterranean Diet [35,49]. 

Semi-structured questionnaires to measure compliance with the consumption of the food products in the food supply were applied every week. The consumption of different products from the same food groups was also assessed.

The nutritional status assessment was realised through the short form of Mini Nutritional Assessment (MNA-SF) [36], previously translated into Portuguese. This screening tool identifies participants that were at risk of malnutrition or malnourished. This tool comprises six questions, scored from zero to three. The maximum total score is 14 points. Participants scoring 0–7 points were considered malnourished, 8–11 points were at risk of malnutrition, and those above 12 points had a normal nutritional status.

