## 2. Design and Methods

The study was designed as a quasi-experimental, 12-week, four-armed, diet and exercise intervention with community-dwelling elderly residents from Porto, Portugal (Figure 1). This protocol report follows the Standard Protocol Items: Recommendations for Interventional Studies (SPIRIT) 2013 checklist [32]. 

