### 2.2. Eligibility and Recruitment

This study included individuals (i) aged 65 years or older, (ii) living in the community, (iii) with independent mobility, (iv) with no past medical history of neuropsychiatric conditions (e.g., major depression or bipolar disease), and (v) with no musculoskeletal or cardiovascular disorders that contraindicate participation in moderate exercise and testing. The exclusion criteria included individuals engaged in regular moderate to vigorous exercise training and followed by a nutritionist.

Eligible participants received a complete explanation of the study’s purposes, risks, and procedures. Before data collection, the principal researcher obtained informed consent from interested participants. After the agreement, participants were assigned into a 3-month SHD, MT, combined SHD and MT (SHD + MT), or control group (CG). 

Participants were assessed at baseline and after 3 months of intervention. At baseline, sociodemographic and economic, lifestyle (e.g., tobacco use and habitual physical activity), and general clinical data were collected through a structured questionnaire. Possible changes in these data were assessed in post-intervention assessments. At these two time points, nutritional and food intake evaluations were obtained through multiple reliable tools [33,34,35]: the Mini Nutritional Assessment [36]; physical capacity assessments through the Senior Fitness Test [37] and handgrip strength; a whole-body Dual X-ray absorptiometry (QDR 4500/A, Hologic Explorer, version 12.4, Bedford, MA, USA); a Montreal Cognitive Assessment [38]; the Quality of Life for Old Module (WHOQOL-OLD) [39]; and accelerometry (ActiGraph GT9X Link, Manufacturing Technology, Inc., South Bend, IN, USA) were performed. 

Participants were only informed about which group they belonged to after baseline assessments. Well-trained and skilled researchers executed the same procedures during the two assessment periods.

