### 2.5. Study Intervention

#### 2.5.1. Sustainable Healthy Diet Group (SHD) 

Diet intervention lasted approximately three months. Participants were provided, weekly, with an SHD food supply, including planted-based foods (nuts and pulses), olive oil, and oily fish, which might have contributed to higher compliance with the overall dietary pattern. Based on the Mediterranean Diet and the latest EAT-Lancet recommendations [12], the individual food supply included per week 125 g of nuts (walnuts, considering a daily serving of 25 g); 350 g of dry pulses (chickpeas and different types of beans, based on a daily serving of 50 g); 280 g of olive oil (a bottle of olive oil was delivered per month); and two servings of oily fish (sardine fillets and tuna, 100 g servings). 

Additionally, the intervention included a total of four sessions: three group sessions (including an SHD culinary workshop) and one telephone interview ranging from 30 (the individual session) to 60 min with a trained nutritionist at the beginning, 1-month, 2-months, and 2.5-months into the intervention. The group and individual sessions were held by nutritionists. The focus was on acquiring knowledge and maximising individual participation. Group sessions involved a maximum of 25 participants. All the sessions were held emphasising participants’ involvement to allow for more dynamic and interactive meetings.

The first group session was an introductory one explaining the principles of an SHD and the benefits of this pattern in several health outcomes. The participants learned how to evaluate environmental impact, and some examples of food footprints were given. The recommended serving sizes of an SHD and the seasonal foods for each month were also presented. 

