### 2.7. Statistical Analyses

Descriptive results will be expressed as median and inter-quartile range (IQR) or mean and standard deviation (SD), as appropriate, for continuous variables. Discrete variables will be presented as counts and percentages. The minimum threshold value for statistical significance used will be *p* ≤ 0.05.

The normality tests, histogram, and plot distribution will assess the normality of data distribution. Comparative analyses between participants and dropouts will be realised by *t*-test or Mann–Whitney U-test for continuous variables and Pearson-Chi Squared or Fisher exact test for categorical variables to determine whether attrition bias was observed. 

Potential differences among intervention groups in baseline measurements will be evaluated using a one-way Analysis of Variance (ANOVA) or correspondent non-parametric Kruskal-Wallis test. A Pearson Chi-squared or Fisher exact test will be used for between-group comparisons of categorical variables. 

Covariates (e.g., sociodemographic and economic characteristics; clinical history, such as the presence of comorbidities; and daily physical activity) were selected a priori and tested. The confounding variables will be entered as covariates in the ANOVA models. For each model, the contribution of all covariates will be tested separately; only the ones that change the magnitude of the association by at least 10% will be included in the final models. The fit of the models will be determined. Whenever necessary, we will use weighted samples to tackle the bias imposed by differential sampling probabilities.

A delta percentage will be calculated to assess the percentage of change between baseline and post-intervention assessments. An ANOVA or correspondent non-parametric test with repeated measures will be performed for differences in main effects and interactions for each dependent variable. When significant interactions are found, Bonferroni posthoc tests will determine the origin of the differences. Multivariable regression analyses will explore the associations between blood-based markers and metabolomics and the secondary outcomes.

Geographical information systems data will be collected. The associations of the primary and secondary outcomes with environmental features will be explored through generalised linear models to understand whether built environment food and PA features lead to statistically significant differences in participants’ dietary and exercise routines.

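### The Food Propensity Questionnaire looks back one year but is repeated after about 12 weeks, so any pre-post change in it is attenuated toward zero

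*Protocol article*

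**What the plan says.** Four statements in the protocol article bear on this point.

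- **Recall window.** Under Dietary Intake Assessment and Nutritional Adequacy (section 2.6.2, Secondary Outcomes), "a Food Propensity Questionnaire [34] was applied to estimate usual and seasonal long-term dietary intake based on the preceding year". No shorter window is given for a second administration.
- **Repetition.** Section 2.2 says "At these two time points, nutritional and food intake evaluations were obtained through multiple reliable tools [33,34,35". Reference 34 is the Food Propensity Questionnaire. The two time points come from the same section: "Participants were assessed at baseline and after 3 months of intervention".
- **Length of the intervention.** Section 2 says "The study was designed as a quasi-experimental, 12-week, four-armed, diet and exercise intervention", and section 2.5.1 says "Diet intervention lasted approximately three months".
- **Analysis.** Section 2.7 says "A delta percentage will be calculated to assess the percentage of change between baseline and post-intervention assessments", and then "An ANOVA or correspondent non-parametric test with repeated measures will be performed for differences in main effects and interactions for each dependent variable". It neither names nor exempts the questionnaire.

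Section 2.6.2 also describes 24-h recalls on two non-consecutive days, the MEDAS score, and weekly questionnaires on consumption of the supplied foods. Energy and nutrient intake is computed from the 24-h recalls.

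**The concern.** A change score is interpretable only if the two measurements refer to different periods. Here they mostly refer to the same one. The baseline questionnaire covers the 52 weeks before the intervention. The follow-up questionnaire covers the last 40 of those weeks plus the 12 weeks of intervention. A participant who changes diet fully on day one and reports accurately will still describe mostly the old diet at follow-up.

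The resulting bias has a known direction: differences between arms in questionnaire change shrink toward zero. The food groups asked about include nuts and pulses, and fish including oily fish, which are foods that the diet arms are given. The loss therefore falls on the contrast that the intervention is meant to create. A null result could be misread as poor dietary uptake and could disagree with the 24-h recalls for no reason except timing. Section 2.7 also plans multivariable regressions relating blood markers and metabolomics to the secondary outcomes, so a mistimed diet variable could enter those as well.

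**Working it through.** The article gives no figure for this point, so there is none to reproduce. The check is time-average arithmetic.

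**Inputs from the document:** recall window of one year (section 2.6.2); intervention of 12 weeks (section 2) or about three months (sections 2.2 and 2.5.1).

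**Step 1. Share of the follow-up window inside the intervention**

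Share = intervention length / recall length; attenuation = 1 / share.

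| Units | Share in intervention | Share before it | Attenuation |
|---|---|---|---|
| 12 of 52 weeks | 23.1% | 76.9% | 4.33-fold |
| 84 of 365 days | 23.0% | 77.0% | 4.35-fold |
| 3 of 12 months | 25.0% | 75.0% | 4.0-fold |

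This assumes a stable diet before the intervention and respondents who average the year evenly.

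**Step 2. Sensitivity to recency**

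Suppose respondents give each intervention week a weight *w* relative to each earlier week. The article says nothing about this, so the weights are assumptions. Share = 12*w* / (12*w* + 40).

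| *w* | Share | Attenuation |
|---|---|---|
| 1 | 12/52 = 0.231 | 4.33-fold |
| 2 | 24/64 = 0.375 | 2.67-fold |
| 3 | 36/76 = 0.474 | 2.11-fold |
| 5 | 60/100 = 0.600 | 1.67-fold |

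The attenuation does not disappear at any of these weights, but its size depends on recall behaviour that nobody has measured.

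**Step 3. Effect on the response categories**

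Under even averaging, the yearly mean at follow-up = (40 × baseline frequency + 12 × intervention frequency) / 52. The baseline frequencies below are assumed; the intervention frequencies follow the food supply.

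- *Pulses.* The supply is "350 g of dry pulses (chickpeas and different types of beans, based on a daily serving of 50 g", that is 350/50 = 7 servings a week. From an assumed 1 per week: (40 × 1 + 12 × 7)/52 = 124/52 = 2.4 per week. The answer falls in the two-to-three-times category, although current intake belongs in the top one (six to seven). A true rise of 6 per week is recorded as about 1.4.
- *Oily fish.* The supply is two servings a week. From an assumed 1 per week: (40 × 1 + 12 × 2)/52 = 64/52 = 1.23 per week. The nearest category is still once a week, so the change can vanish.

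Because the seven response options are ordinal, the loss is uneven: some real changes are shrunk and others are not recorded at all.

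**Step 4. If the windows matched**

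With a follow-up window equal to the 12-week intervention, the share would be 100% and the attenuation 1.0.

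**The case against.** The strongest reply is that the article never says that change in this questionnaire will be tested. Section 2.7 speaks generically, and section 2.6.2 presents the questionnaire as a supplement to the 24-h recalls, aimed at habitual intake over a long period. Used as a descriptor or as a frequency input to the recalls, it would do no harm. Repetition is also stated through a citation number rather than by name, and which variable enters which model is often settled in a fuller document. This stands in part: the plan is open on the point rather than explicit. But it places the questionnaire among secondary outcomes, applies it at both time points and plans change tests for every dependent variable without exception. A reader following the text would test its change.

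The second reply concerns consequence. The primary outcomes are blood biomarkers and metabolic alterations, and diet is also measured by other tools. Attenuation in one secondary measure would hide an effect rather than create one. This stands, and it limits the weight of the point.

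Three stronger readings are tempting but not supported:

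- *That the questionnaire cannot register change, or that fourfold is an established figure.* Some change is still captured, and fourfold holds only under even averaging.
- *That about 19 times the sample would be needed* (1/0.230² = 18.9). This requires the standard deviation of change to stay the same while its mean shrinks, on an ordinal scale treated as continuous. The article gives no basis for that, and its sample size is not tied to this questionnaire.
- *That a mediation analysis would be distorted.* None is planned; section 2.7 speaks only of exploring associations by regression.

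**Conclusion.** The point holds as a limited one about a single secondary measure. With a one-year window and a 12-week interval, 75 to 77% of what is reported at follow-up predates the intervention, and a pre-post change is biased toward zero. That share follows directly from the document. The size of the attenuation does not: it is about 4.0- to 4.35-fold under even averaging, and about 2.7- to 1.7-fold if intervention weeks count 2 to 5 times as much.

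The conclusion rests on two readings of the text: that the citation in section 2.2 means the questionnaire was given twice with the same window, and that the generic change analyses in section 2.7 include it. Nothing in the article contradicts either. The two-month exercise adaptation period does not alter the result, because the diet intervention is stated separately as about three months.

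**What to change.** Section 2.1 says that data collection has ended, so the recall window cannot be changed, but the analysis can. Add a statement to section 2.7 that:

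1. the Food Propensity Questionnaire serves as a baseline descriptor, or a covariate, of usual intake;
2. its pre-post change is excluded from the tests of intervention effect and from the regressions with blood markers and metabolomics;
3. diet change is taken from the 24-h recalls, MEDAS and the weekly food-supply questionnaires;
4. any three-month questionnaire values that are reported are labelled as covering the preceding year.

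On item 3, the weekly questionnaires concern the supplied foods and so inform mainly on the diet arms. The contrast with the control group would rest on the 24-h recalls and MEDAS. The article does not state a reference period for MEDAS, so it should be confirmed.

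The cost is one sentence and one fewer diet-change outcome. No new data are needed.

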##### Physical Fitness

Physical fitness was assessed by the Senior Fitness Test (SFT) [37], a trustworthy method for assessing physical capacity in the elderly that includes six functional tests: (i) the chair stand test, which reflects lower body strength, measured for 30 s; (ii) the arm curl test, to measure upper body strength for 30 s; (iii) the six-minute walk test, to assess aerobic endurance; (iv) the chair sit and reach test, to measure lower body flexibility; (v) the back scratch, that assesses the upper body flexibility; and (vi) the time up-and-go test. 

Static balance was also measured with the One Leg Balance Test [50]. In this test, the participant stood unassisted on one leg and the maximum time (45 s) reached, in seconds, from the moment one foot was off the floor to the moment it touched the other leg or the ground was registered. The participant was allowed three attempts, and the best result was recorded.

Finally, handgrip strength was obtained with a digital Jamar hand dynamometer (Sammons Preston Inc., Illinois, IL, USA). According to the American Society of Hand Therapists [51], individuals sat comfortably in a chair without armrests with the shoulder in adduction and neutral rotation, the elbow in 90° flexion, and the forearm and wrist in a neutral position, between 0° and 30° of dorsiflexion. In the handgrip strength test, participants performed three trials at one-minute intervals with each hand (information on the dominant hand was recorded). 

##### Body Composition and Anthropometry

Body composition was analysed through DXA (QDR 4500/A, Hologic Explorer, version 12.4, Bedford, MA, USA), a valid and reliable method in the elderly population for whole-body lean and fat mass, body fat percentage, and trunk fat, with subjects in the supine position.

Anthropometric measurements were taken using international standardised protocols. Body Mass Index (BMI) was determined to the nearest 0.1 kg with an electronic portable weight scale (Inbody 120, Seoul, Republic of Korea). Overweight and obesity will be defined using international criteria [52]. Waist and hip circumference were assessed using a spring-loaded measuring tape parallel to the floor. Waist circumference was measured at the midpoint between the iliac crest and the bottom of the ribcage and the hip circumference at the broadest portion of the buttocks [53].

##### Cognitive Function

The Montreal Cognitive Assessment (MoCA) [38,54], previously translated into Portuguese, a commonly used cognitive function test among older adults, was applied. It is a brief test, scored to a maximum of 30 points, with higher scores reflecting better cognitive performance. The MoCA assesses several cognitive domains. Visuospatial capabilities were evaluated through a clock-drawing task (3 points) and a 3D cube copy (1 point). Executive functions were assessed using a task adapted from the Trail Making B task (1 point), a phonemic fluency task (1 point), and a two-item verbal abstraction task (two points). The short-term memory recall task (5 points) involved two learning trials of five nouns and a delayed recall after approximately 5 min. Attention, concentration, and working memory were evaluated using a sustained attention task (1 point), a serial subtraction task (3 points), and digits forwards and backwards (1 point each). The language domain was measured using a three-item animal naming task (3 points) and the repetition of two syntactically complex sentences (2 points). Temporal and spatial orientation was evaluated to a total of 6 points.

##### Quality of Life

The Quality of Life for Old Module (WHOQOL-OLD) [39] was used to measure the participants’ quality of life. The WHOQOL-OLD module consists of 24 items categorised into the following six domains, answered on a 1–5 Likert scale: sensory abilities; autonomy; past, present, and future activities; social participation; death and dying; and intimacy. Higher scores reflect a greater quality of life.

##### Geographical Data

Geographical data will be gathered using several data sources and systematised in a geodatabase in ArcGIS, version 10.5 (Environmental Systems Research Institute, California, USA). The variables’ selection criteria were based on previous literature and included walkability and access to green spaces, fast-food restaurants, grocery and convenience stores, and supermarkets. To measure pedestrian access, we will use a 400-m street-network buffer as a reasonable walking distance to neighbourhood resources.

#### 2.6.3. Confounders

As possible confounders, we will control at baseline and after the intervention for (i) sociodemographic and economic status, (ii) clinical history, (iii) tobacco use, (iv) medication (collected through a structured questionnaire), and (v) daily physical activity, assessed through an accelerometry-based method (ActiGraph GT9X Link, Manufacturing Technology, Inc., South Bend, IN, USA). Participants were instructed to always wear the accelerometer for seven consecutive days attached to an elastic belt, except when sleeping or during water activities. Data were collected in 100 Hz epochs; valid data must include a minimum of 10 h on at least four days (with one weekend day). This data will be processed using Actilife™ software, version v6.13.4 (Actigraph LLC, Pensacola, FL, USA) and organised as sedentary, light, moderate, and vigorous physical activity.

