### 2.3. Sample Size Estimation

The sample size was estimated based on previous literature and the ANCOVA to analyse the differences between and within groups [40]. A sample size calculation was conducted using G*Power 3.1.3 (Universität Düsseldorf, Düsseldorf, Germany) [41]. We predicted the inclusion of 25 participants per group, a total of at least 100 community-dwelling older adults, both men and women, considering a moderate effect size of 0.40, an alpha-risk of 0.05, and a beta-risk of 0.20 in a 2-sided test, and anticipating a 20% dropout rate.

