Some challenges to this study must be recognised. Firstly, we anticipate a potential sample with several age-related comorbidities. Secondly, the elderly tend to mainly adopt sedentary behaviours, increasing difficulties in the recruitment process. Based on differences in baseline participant characteristics, a misinterpretation of the primary outcomes and an inability to generalise the results may occur. Considering the main inclusion criteria, the different interventions cannot be generalised to other specific populations. Despite including participants with lower nutritional status or who were inactive, we cannot exclude the possibility that the participants involved in the study were more prone to healthy lifestyle behaviours. Though, this bias was minimised by excluding participants that were engaged in regular physical activity or consulting a nutritionist. Additional research will help identify the most effective diet and exercise intervention protocols for more heterogeneous, non-uniform, and other specific population groups. A cross-over and randomised controlled trial (RCT) design, where the same participant implemented different interventions, would reduce the likelihood of heterogeneity affecting the evaluation of primary outcomes. Initially, our study protocol was thought and designed to be a cross-over RCT. Although, the methodology needed to be adapted due to the beginning of the unpredictable pandemic situation, which occurred simultaneously with the start of the recruitment study and disabled the sample randomisation. The pandemic situation delayed and imposed logistical difficulties in the recruitment process. The lockdown and isolation of this at-risk population group (older adults) affected baseline assessments and the study intervention due to the closure of facilities.

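### The confounder list of this non-randomised diet and exercise trial names daily physical activity but not baseline diet, which is measured and could confound the two diet-arm contrasts

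*Protocol article*

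**What the plan says.** - **Allocation.** The Discussion says that the pandemic "disabled the sample randomisation". The study is quasi-experimental with four arms: SHD, MT, SHD + MT and control.
- **Confounders.** Section 2.6.3 opens: "As possible confounders, we will control at baseline and after the intervention for (i) sociodemographic and economic status, (ii) clinical history". Items (iii) to (v) are tobacco use, medication and accelerometer-measured daily physical activity. The list is numbered and has five items; diet is not one of them.
- **Covariates.** Section 2.7 gives examples of covariates chosen in advance: sociodemographic and economic characteristics, clinical history and daily physical activity. Diet is not named. Only covariates that change the association by at least 10% stay in the final model.
- **Entry.** Section 2.2 states: "The exclusion criteria included individuals engaged in regular moderate to vigorous exercise training and followed by a nutritionist". No criterion concerns what a person eats.
- **Diet is measured.** Food intake is assessed at baseline and at 3 months (section 2.2). The tools in section 2.6.2 include MEDAS, on which "scores greater than 9 indicate high adherence to the Mediterranean Diet".
- **Analysis.** Section 2.7 plans a repeated-measures ANOVA (or non-parametric equivalent) with interactions, a percentage change from baseline, and tests of baseline differences between groups.
- **Claim about bias.** The Discussion concedes that participants may have been more inclined to healthy habits, then adds: "this bias was minimised by excluding participants that were engaged in regular physical activity or consulting a nutritionist".

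**The concern.** The plan treats the two target behaviours differently. Daily physical activity is listed for adjustment. Diet is not, and its only gatekeeper at entry is nutritionist follow-up, which says nothing about intake. A volunteer with a MEDAS score above 9 can enter any arm.

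In a randomised trial this would matter little. Here nothing in the design makes the arms alike in diet, and the Discussion, when it describes the sample as similar at baseline, mentions physical activity and sociodemographic and economic conditions but not diet. Baseline diet plausibly affects how far lipids, glucose, hs-CRP, vitamin B12 and the metabolic profile can move over three months. If the diet arms started with better or worse diets than the comparison arms, part of the difference in change would be wrongly credited to the intervention or hidden from it.

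**Working it through.** **1. The planned sample size, for scale.** Section 2.3 plans 25 participants per group (at least 100 in all) and allows for 20% dropout. Its effect size and error rates read: "considering a moderate effect size of 0.40, an alpha-risk of 0.05, and a beta-risk of 0.20 in a 2-sided test". Reading 0.40 as Cohen's f (an assumption), with 4 groups, 3 numerator degrees of freedom and noncentrality f² × N:
- smallest N for 80% power: 73, i.e. 73/4 = 18.25, rounded up to 19 per group
- with 20% dropout: 19/0.80 = 23.75, i.e. 24 per group against the 25 stated, so the plan's figure is reproduced to within one participant per group
- expected completers: 25 × 0.80 = 20 per arm, 80 in all; power at 80 is 84.5%

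**2. What remains after the repeated-measures analysis.** Let Y0 and Y1 be a biomarker before and after, and D the baseline diet score. If D shifts Y0 and Y1 equally, it cancels from Y1 − Y0 and hence from the group-by-time interaction. What does not cancel is any effect of D on Y1 − Y0 itself. The relevant correlation r is therefore that between D and *change*, not between D and the outcome level.

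**3. Size of the possible bias.** Bias in a contrast = r × d, in SD of change, where d is the difference between arms in baseline MEDAS in SD units. The documents give neither, so both are assumed. The last two columns show the true type I error of a nominal two-sided 5% test of change.

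| r (assumed) | d (assumed) | Bias = r × d | 20 v 20 | 40 v 40 |
|---|---|---|---|---|
| 0.2 | 0.5 | 0.10 SD | 6.1% | 7.3% |
| 0.3 | 0.5 | 0.15 SD | 7.5% | 10.2% |
| 0.4 | 0.5 | 0.20 SD | 9.5% | 14.3% |

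The 20 v 20 column is one arm against another; 40 v 40 is the two diet arms pooled against the other two. Over a wider range (r 0.1 to 0.5, d 0.2 to 0.8) the bias runs from 0.02 to 0.40 SD, so it can also be negligible.

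**4. Would the planned baseline test reveal such an imbalance?** Suppose one arm differs from the other three by 0.5 SD. The mean is 0.5/4 = 0.125, so f² = [(0.375)² + 3 × (0.125)²]/4 = 0.0469 and f = 0.217. The four-group ANOVA then has 40% power with 25 per arm and 32% with 20 per arm. A non-significant result would not show balance, and the article ties no action to a significant one.

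**5. Price of the adjustment.** With one covariate, the required N stays at 73 and power with 80 completers stays at 84.5%.

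**The case against.** The strongest reply has four parts.

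- **The covariate list in section 2.7 is open, and this is a condensed article.** True, and a fuller plan may name diet. But section 2.6.3 is a numbered list without such an opening. Leaving diet to be added later, after the data are seen, is what a list chosen in advance should prevent. The 10% rule does not help, because it can only keep a variable that has been put forward.
- **Repeated measures already use each outcome's own baseline.** This stands and narrows the point: stable effects of diet on biomarker level drop out, and confounding acts mainly through change.
- **The authors admit the limitation.** They do say that healthy-lifestyle selection cannot be excluded and that baseline differences may mislead. The sentence that follows, saying that the bias was minimised, is nonetheless too strong for diet.
- **No imbalance has been shown.** This stands. The article gives no baseline diet by arm.

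Two stronger readings are tempting, and the documents support neither. A reader might infer that the diet effect is biased because some participants already eat well. But an average effect in all community-dwelling elders, good eaters included, is a legitimate target; a smaller effect in that population is not a bias, and the share of high adherers is not given. A reader might also infer that the entry criteria tilt a diet-versus-exercise comparison towards exercise. Section 2.2 excludes people in regular moderate to vigorous training; it does not screen for inactivity, so someone with high daily activity can enter. Without the room for improvement on either side, no direction follows.

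**Conclusion.** The point holds as an omission with a credible but unmeasured consequence. Baseline diet is absent from the confounder list and from the covariate examples of a non-randomised trial in which diet is an intervention target, and nothing else in the article secures its adjustment. The SHD and SHD + MT contrasts could be confounded, mainly through change; 0.10 to 0.20 SD is the size under the assumed 0.5 SD imbalance and correlation of 0.2 to 0.4 with change. Those inputs are illustrations, not findings. That diet is unlisted and unscreened is certain from the text; whether the arms differ in diet, and in which direction, is not known. The change is worth making because the data are already collected and the cost is close to nil.

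**What to change.** 1. Add baseline MEDAS score to the list in section 2.6.3. Enter it as a prespecified covariate in all primary-outcome models, kept regardless of the 10% rule. In the repeated-measures models it must enter with its interaction with time, since that is the term that adjusts change. Use the baseline value only: diet after the intervention is part of what the intervention is meant to alter.
2. Report baseline MEDAS by arm (mean and SD, and the share above 9), and judge balance on the size of the differences rather than on a p-value.
3. Qualify the Discussion's statement that the exclusions minimised healthy-lifestyle bias: dietary pattern was not screened at entry and is dealt with by adjustment.
4. If an interaction of the diet intervention with baseline MEDAS is wanted, keep the score continuous and label the analysis exploratory. A split at 9 with about 20 completers per arm would be too small to inform.

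The cost is some wording and one degree of freedom per model. Eligibility cannot be changed, since data collection ended in December 2022, and need not be.
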